### Secondary outcomes

The most important secondary outcome is postoperative time to functional recovery. Functional recovery, as defined by a previous RCT [19, 20], is reached when all of the following criteria are met: (I) adequate pain control with oral analgesia only; (II) restoration of mobility to an independent level (or to preoperative level if previously impaired); (III) ability to maintain sufficient caloric intake (minimum of 50% required calories); (IV) absence of intravenous fluid administration; (V) no signs of active infection (no fever, decreasing C-reactive protein below 150 mg/L).

Post-operative activity will be measured using a Fitbit™ Inspire 2, by patients on their wrists (1–2 weeks) from prior to surgery to 90 days after surgery [26–29]. A comprehensive overview of the outcomes of the postoperative activity tracking will be described as a separate publication.

Other secondary outcomes of this trial include intra-operative parameters (type of surgery (laparoscopic or robot-assisted), conversion (urgent or non-urgent), method of anastomosis, vessel resection, operative time, blood loss, and blood transfusion), postoperative outcomes (up to 90 days after surgery; major complications (defined as a Clavien-Dindo grade III or higher) and mortality (and whether related to surgery), postoperative pancreatic fistula [30], post-pancreatectomy hemorrhage [31], delayed gastric emptying [32], chyle leak [33], surgical site infection [34], postoperative intervention (surgical, radiologic or endoscopic), intensive care unit admission, (multi) organ failure, length of hospital stay, readmission, (time to) start of adjuvant therapy) and pathological outcomes (pathological diagnosis, tumor size, histology and tumor grading [35], distance from the tumor to all margins, number of retrieved lymph nodes, number of positive lymph nodes, lymphovascular and perineural tumor invasion, and venous and arterial tumor involvement). For the economical evaluation, costs (intra-operative and postoperative costs (up to 90 days)) and quality of life (using the validated EQ-5D-5L, QLQ-C30, and PAN-26 questionnaires with additional questions regarding scar complications and body image (up to 3 years)) are compared [36, 37].

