### Statistical aspects

#### Sample size calculation

The DIPLOMA-2 trial is designed as a non-inferiority trial, hypothesizing that the mean CCI® score of MIPD is non-inferior to OPD. Calculations are based on results of the pan-European E-MIPS retrospective cohort study and on individual patient-data collected from the previous conducted RCTs on MIPD versus OPD. The sample size is calculated using PASS 2022 software to achieve 80% power (1-β) in a per-protocol analysis with the following assumptions: 2.5% one-sided significance level (α), expected difference of the mean CCI® score in the MIPD and OPD group of 0 points, and a non-inferiority margin of 7.5 points, standard deviation of 20 points in both groups, including 5% metastasized disease, a 10% conversion rate and a 3% lost-to-follow-up rate after randomization leads to a total number of patients to be randomized of 288 (192 in the MIPD study arm and 96 in the OPD study arm). For time to functional recovery, we assume MIPD will result in a reduction of 2 days (7 days in the MIPD group versus 9 days in the OPD group. Time to functional recovery will be measured in days and will be tested for superiority using the Wilcoxon (Gehan-Breslow) test or the log-rank test (based on non-normal distribution). With a one-sided testing, assuming 5% metastatic disease, 10% conversion rate, and 3% loss to follow-up, a sample of 247 patients (159 in the MIPD group and 88 in the OPD group) in a per protocol analysis achieves 80% power to detect a 28% reduction of time to functional recovery (i.e., 6.5 days in the MIPD group; hazard ratio = 0.72). The estimated median time to functional recovery of 9 days in the OPD group is based on results of the LEOPARD-2 trial and corresponds to a median TTFR reduction of 2.5 days.

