The primary outcome measure “CCI®” will be expressed as means (standard deviations) or medians (interquartile ranges) and will be tested for non-inferiority using independent samples *t*-test or Mann–Whitney *U* test, as appropriate dependent of the distribution. The most important secondary outcome measure “time to functional recovery” will be measured in days and will be tested for superiority using the Wilcoxon (Gehan-Breslow) test or log-rank test, depending on the distribution. Secondary analysis will include correction for censored patients (death before time to functional recovery obtained). For the primary study outcome, the lower limit of the two-sided 95% confidence interval of the difference in proportions will be reported and compared with the non-inferiority margin. Additionally, the individual functional recovery criteria will be analyzed separately. Major complications, expressed in proportions, will be tested for non-inferiority using chi-square or Fisher’s exact test as appropriate. The distribution of variables will be determined using several plots (boxplot, Q-Q plot and histogram) and the Kolmogorov–Smirnov and Shapiro–Wilk tests. For comparison of normally distributed continuous variables, the independent samples *t*-test will be used, and values will be expressed as means (standard deviations). Continuous non-normally distributed variables will be compared using the Mann–Whitney *U* test, and values will be expressed as medians (interquartile ranges). Categorical variables will be compared by chi-square or Fisher’s exact test as appropriate, and values will be expressed as proportions. A two-tailed *p*-value < 0.05 will be considered statistically significant. Time to event endpoints, such as survival, will be calculated using Kaplan–Meier estimations. A Cox regression analysis will be performed to investigate predictors of postoperative survival. All parameters with a *p*-value < 0.1 in a univariable analysis will be included in the multivariable Cox regression analysis. Additionally, multivariable analyses will be performed to determine predictors for primary and secondary study outcomes, for example the occurrence of major complications, postoperative pancreatic fistula, and R0 resection. Furthermore, predictors for receiving adjuvant chemotherapy or readmission will be assessed.

For subjects who are lost to follow-up, a sensitivity analysis will be performed to determine best case/worst case scenarios.

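### Major complications are to be tested for non-inferiority with chi-square or Fisher's exact tests, which test equality and have no margin on the proportion scale

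*Protocol article*

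**What the plan says.** The Statistical analysis section of the protocol article states: "Major complications, expressed in proportions, will be tested for non-inferiority using chi-square or Fisher’s exact test as appropriate". The same section gives these tests the ordinary role of comparing groups, "Categorical variables will be compared by chi-square or Fisher’s exact test as appropriate, and values will be expressed as proportions", and sets one general criterion: "A two-tailed *p*-value < 0.05 will be considered statistically significant".

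The only margin in the article is in the Sample size calculation (and repeated in the Abstract): "and a non-inferiority margin of 7.5 points, standard deviation of 20 points in both groups". It refers to the mean CCI, the primary outcome. The only rule that compares a confidence limit with a margin reads "For the primary study outcome, the lower limit of the two-sided 95% confidence interval of the difference in proportions will be reported", and it too is assigned to the primary outcome.

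Major complications are Clavien-Dindo grade III or higher up to 90 days. Under Secondary outcomes they are listed among the other secondary outcomes. The most important secondary outcome is time to functional recovery. No event rate, margin or power is stated for major complications.

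**The concern.** The stated aim and the stated method do not match. A chi-square or Fisher's exact test asks whether two proportions differ. Rejection shows a difference. Non-rejection shows only that the data do not rule out equality, and they may equally fail to rule out a large excess. Neither outcome answers the question of non-inferiority, which is whether an excess as large as a fixed margin can be excluded. The one exception is a significant result in favour of MIPD, because the interval for the excess then lies below zero and so below any positive margin.

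This matters because the trial is designed primarily to investigate the safety of MIPD in terms of morbidity and mortality (Background). Apart from the primary CCI, major complications are the only outcome that the article says will be tested for non-inferiority. A non-inferiority statement on severe complications would carry weight with readers, and the named tests could not support it unless MIPD came out significantly better.

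**Working it through.** **1. The plan's own figure.** The article gives a sample size only for the CCI. Applying its attrition rates by arm, with conversion in the MIPD arm only:
- MIPD: 192 × 0.95 × 0.90 × 0.97 = 159
- OPD: 96 × 0.95 × 0.97 = 88

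These are the per-protocol numbers in the article. With SD 20 and margin 7.5, SE = 20 × √(1/159 + 1/88) = 2.657. Power = Φ(7.5/2.657 − 1.96) = Φ(0.862) = 80.6%, or 80.3% by the noncentral t. The 288 patients therefore reproduce, but for the CCI only.

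**2. Inputs for major complications.** The numbers per arm come from the article: 192/96 randomized and 159/88 per protocol. These bracket the modified intention-to-treat set. The event rates are assumptions, because the article gives none. The test is the uncorrected chi-square at two-sided 5%.

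**3. How often the named test is non-significant when MIPD is truly worse.** One case by normal approximation: 40% (MIPD) vs 30% (OPD) at 192/96.
- Pooled rate: (192 × 0.40 + 96 × 0.30)/288 = 0.3667
- SE under equality: √(0.3667 × 0.6333 × (1/192 + 1/96)) = 0.0602
- Largest non-significant difference: 1.96 × 0.0602 = 0.1181
- SE at the true rates: √(0.40 × 0.60/192 + 0.30 × 0.70/96) = 0.0586
- P(non-significant) ≈ Φ((0.1181 − 0.10)/0.0586) = Φ(0.31) ≈ 62%

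Exact binomial enumeration gives:

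| True rates, MIPD vs OPD (assumed) | 192/96 | 159/88 |
|---|---|---|
| 40% vs 30% | 61.6% | 66.0% |
| 45% vs 35% | 63.4% | 66.4% |
| 35% vs 30% | 86.8% | 88.3% |

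Fisher's exact test is slightly more often non-significant, for example 63.5% at 40% vs 30% with 192/96.

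**4. A single result.** Take 80/192 (41.7%) on MIPD and 29/96 (30.2%) on OPD, a difference of 11.5 points. Chi-square gives p = 0.059 and Fisher p = 0.071, so neither is significant. The 95% Wald interval is 0.115 ± 1.96 × 0.0588, or −0.1 to +23.0 points. The data leave open an excess of 23 points.

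**5. What a margin rule would do.** Under this rule non-inferiority is declared when the upper 95% Wald limit for MIPD minus OPD lies below the margin. The figures are for 192/96, with assumed OPD rates of 25% to 40% and illustrative margins.
- MIPD truly 10 points worse, margin 10 points: declared in 2.2% to 2.3% of trials.
- Power when the arms are truly equal: 13% to 14% at 5 points, 37% to 45% at 10 points, 69% to 80% at 15 points.
- Total number of patients for 80% power at 2:1: 2649 to 3393, 663 to 849 and 297 to 378 respectively.

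At 159/88, power for a 10-point margin is 33% to 41%.

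**The case against.** A reader might infer that the plan will let a non-significant difference pass as proof of safety. The article does not say this. It contains no rule that p above 0.05 means non-inferior, and the only non-inferiority rule it states, for the primary outcome, compares a confidence limit with a margin. The percentages in step 3 therefore describe what would follow from such a reading. They are not a documented error rate of this plan.

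It is also tempting to call this the central safety outcome. The article does not rank it so. Its safety claim rests on the CCI, which accumulates all complication grades, has a margin and is powered, and a data safety monitoring board meets after every 50th patient completes 90 days. A poorly matched test on one secondary outcome does not decide the trial.

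Two further arguments stand in part. First, a detailed statistical analysis plan was to follow before database lock, and a margin for a secondary outcome could properly be set there, so the missing margin alone would not be a finding. The article nevertheless names the test, and supplying a margin would not turn an equality test into a non-inferiority test. Second, the confidence-interval sentence speaks of a difference in proportions, which fits major complications better than a score. A confidence-limit approach to this outcome may have been intended and the wording garbled. As written, however, the sentence concerns the primary outcome, and no margin on the proportion scale exists for it to use.

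**Conclusion.** The concern holds as a mismatch between method and objective. The article announces a non-inferiority test of major complications and names tests of equality, with no margin or confidence-limit rule that applies to this outcome. They can support the announced conclusion only when MIPD is significantly better.

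If non-significance were taken as non-inferiority, a true 10-point excess would pass in about 62% to 66% of trials in the cases examined, and a 5-point excess in about 87% to 88%. These figures rest on assumed event rates of 30% or 35% on OPD, two-sided 5% testing, and patient numbers between the randomized and per-protocol totals. The mismatch itself depends on none of these assumptions. The point should be corrected, but it concerns one secondary outcome and leaves the primary analysis untouched.

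**What to change.** Replace the sentence with: *The risk difference (MIPD minus OPD) in major complications will be reported with a two-sided 95% confidence interval (Miettinen-Nurminen or Newcombe).* Then choose one of two courses:

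- **Drop the word non-inferiority for this outcome.** This is the realistic course, since under the assumed rates power is below 50% for any margin of 10 points or less.
- **Keep it**, with a justified risk-difference margin fixed before database lock, and claim non-inferiority only if the upper confidence limit lies below that margin.

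The change takes one sentence in the statistical analysis plan and needs no further patients or data. The price is that the statement on major complications becomes an estimate with its uncertainty, and not a non-inferiority claim, unless a margin is set.

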### Data collection and patient follow-up

Baseline characteristics (age, sex, performance status (Karnofsky score [38]), ASA physical status, body mass index, previous abdominal surgery, preoperative diabetes mellitus, preoperative imaging conclusion including tumor size and involvement of other organs and vessels, neo-adjuvant treatment, serum levels of Hba1C, CA 19.9 and CEA, and baseline quality of life questionnaires’ scores will be recorded before intervention. All required clinical data will be collected after randomization (i.e., from hospitalization up to 36 months postoperatively) using standardized online case report forms by the local treating physicians and will be crosschecked with source data by the study coordinators at 3 and 36 months after the last patient is enrolled. To assess postoperative daily activity (up to 90 days), this study uses the Fitbit™ Inspire 2 to record step counts (as a measure of physical activity), and heart rate, combined as “active minutes” per day. For quality-of-life measurements, the validated questionnaires will be sent (electronically) to participating patients at baseline and at 1, 3, 6, 12, and 36 months after surgery. Patients will also receive an additional questionnaire at 6 months focusing on possible complications with the scar and body image. Patients will be followed at the outpatient clinic according to local protocols (including abdominal CT scan and serum levels of CA 19.9 and CEA tumor markers, if indicated). In each center, a monitor visit is performed 90 days after the last included patient has undergone surgery to cross-check primary and secondary outcome data.

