## Discussion

The DIPLOMA-2 trial is an international randomized controlled, patient-blinded trial assessing the non-inferiority of MIPD compared to OPD regarding overall complications in patients with any pancreatic and peri-ampullary neoplasm. The study was carefully designed and initiated by the European Consortium on Minimally Invasive Pancreatic Surgery (E-MIPS), to ensure the generating of high-quality data that can be used to guide clinical practice and improve patient outcomes. The DIPLOMA-2 trial will represent a significant advancement in the field of pancreatic surgery, as it is the first international multicenter patient-blinded randomized controlled trial comparing MIPD with OPD for premalignant and malignant disease.

To date, four randomized studies on L-MIPD versus OPD have been published, of which two single center studies, and two multicenter studies [4–7]. Three studies reported that LPD was safe and feasible, with lower blood loss, shorter hospital stay, and faster recovery with similar mortality and mortality, as compared to OPD. However, the LEOPARD-2 trial was terminated early because of a trend towards higher mortality rate in the L-MIPD group (5 (10%) vs 1 (2%), *P* = 0.20) which raised questions regarding the safety of this approach. This led to a reduction in the use of L-MIPD worldwide and ever since the question of the safety of MIPD versus OPD remained a topic of debate [41]. For this reason, the E-MIPS consortium collectively decided that in order to safely and validly expand MIPD worldwide, a new large international multicenter trial in experienced high-volume centers with strict quality standards was needed, with the necessary modifications to the design.

For this reason, the primary outcome of the DIPLOMA-2 trial is overall complications, measured using the CCI®. This choice was based on the various (online) meetings with all principal investigators involved, where there was consensus on safety as the most clinically relevant endpoint for patients undergoing MIPD. By focusing on cumulative complications, the trial aims to capture a comprehensive picture of the safety and efficacy of MIPD compared to OPD. Because the expected benefits of MIS lie in the reduction of surgical impact, and therefore enhanced postoperative recovery, the trial is also powered to assess superiority of time to functional recovery, as a most important second outcome measure.

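### The only analysis rule that would cover quality of life is an unadjusted two-sample test, which leaves the baseline score, the strata and the repeated measures unused; the late scores also need a while-alive label

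*Protocol article*

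**What the plan says.** Quality of life is listed as a secondary outcome in the Abstract. In Secondary outcomes it appears in the sentence on the economic evaluation, which ends "questionnaires with additional questions regarding scar complications and body image (up to 3 years)) are compared". Data collection and patient follow-up gives the schedule: "at baseline and at 1, 3, 6, 12, and 36 months after surgery".

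Statistical analysis names no method for these scores. Its general rule is "For comparison of normally distributed continuous variables, the independent samples" t-test, and "Continuous non-normally distributed variables will be compared using the Mann–Whitney" U test, at a two-tailed 5% level. No covariates are mentioned.

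Death is dealt with for two other outcomes. It scores 100 on the CCI (Primary outcome) and is treated as censoring in a secondary analysis of time to functional recovery (Statistical analysis). The best-case/worst-case sensitivity analysis is for patients lost to follow-up. For quality of life after death nothing is said. Survival is to be estimated by Kaplan–Meier. A detailed SAP is announced at the end of the analysis sections, to be written before database lock of the outcomes up to 90 days; it is not shown.

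**The concern.** A reader who follows the published text would run a separate two-sample test on each scale at each visit. That sets aside three things the trial already has: each patient's own baseline score, the factors used to stratify the randomisation (minimally invasive technique, fistula risk, PDAC or other indication), and the link between successive scores from one patient. The price is wider intervals for an outcome on which the minimally invasive approach may be judged.

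There is a further point of interpretation. The population includes pancreatic cancer and the last questionnaire is at 36 months. A 36-month score exists only for patients who are alive and respond, so a test on observed scores compares survivors, and the article does not say so.

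**Working it through.** **The plan's own figures.** The article gives no SD, effect, power or sample size for quality of life, so there is nothing to reproduce. Only the arm sizes, 192 and 96, are taken from Sample size calculation.

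**Step 1: precision lost by ignoring baseline.** With a linear adjustment for a baseline score that has correlation *r* with the follow-up score:

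- variance (adjusted) / variance (unadjusted) = 1 − *r*²
- *r* = 0.4: 1 − 0.16 = 0.84, a reduction of 16%
- *r* = 0.6: 1 − 0.36 = 0.64, a reduction of 36%

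The range for *r* is an assumption. In SD units, with all patients responding:

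- unadjusted SE = √(1/192 + 1/96) = 0.125; 95% half-width = 1.96 × 0.125 = 0.245
- *r* = 0.4: 0.245 × √0.84 = 0.225
- *r* = 0.6: 0.245 × √0.64 = 0.196

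Intervals would thus be about 8% to 20% narrower. Put another way, 288 patients with adjustment are worth 288/0.84 = 343 to 288/0.64 = 450 without it. The ratios do not depend on the number who respond. They apply to the t-test and only approximately to the Mann–Whitney test. Any gain from the strata or the repeated measures would be additional, but the article gives nothing from which to size it.

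**Step 2: what survivor selection could do, as illustration only.** The article gives no 36-month mortality, no SD for quality of life and no link between quality of life and survival. Suppose quality of life would be the same in both arms if nobody died, and let ρ be its correlation with a latent survival score, so that the fraction *p* with the lowest survival score die.

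- survivor mean (SD units) = ρ × φ(c)/(1 − *p*), with c = Φ⁻¹(*p*)
- *p* = 0.30: φ(c)/(1 − *p*) = 0.497; *p* = 0.40: 0.644; *p* = 0.50: 0.798
- deaths 30% in both arms: difference 0; chance of a false result favouring MIPD stays at 2.5%
- ρ = 0, any mortality: difference 0; 2.5%
- OPD 30%, MIPD 40%: 0.147ρ, that is 0.04 SD (ρ = 0.3) to 0.07 SD (ρ = 0.5); 4.8% to 7.4%
- OPD 30%, MIPD 50%: 0.301ρ, that is 0.09 to 0.15 SD; 8.4% to 17.4%

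The false-positive chances take 192(1 − *p*) and 96(1 − *p*) survivors, all responding, with the variance among survivors under the same model. Every mortality and ρ value is assumed. The mechanism needs both unequal mortality and a link between quality of life and death, and it is small for a 10-point mortality difference.

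**The case against.** The strongest reply is that the article never says quality of life will be analysed with these tests. The rule is generic, and the quality-of-life comparison sits within the economic evaluation. The longitudinal model, the covariates and the handling of deaths are matters that a condensed article normally leaves to the SAP. Much of this stands. The point therefore cannot be that the article assigns the wrong test to quality of life, or that it is at fault for lacking a death rule. What remains is that the only rule in the text that reaches these scores is unadjusted, so the SAP has to set it aside and not merely add detail. The SAP's drafting is also tied to the 90-day lock, so the article does not by itself show that 36-month quality of life will be covered.

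It is also fair to say that an unadjusted comparison in a randomised trial is valid. The loss is of precision only.

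A reader might infer more: that survivor-only scores will make MIPD look better, with the mortality contrast quoted in the Discussion as the size of the problem. The documents do not support that. The contrast is 5 (10%) against 1 (2%) deaths, P = 0.20, in an earlier laparoscopic trial that stopped early. It says nothing about mortality at 36 months or in the robotic centres included here. The SD of 20 in the sample size section belongs to the CCI. A real excess of deaths would also show in the CCI, in 90-day mortality, in the survival curves and in the safety board's reviews.

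**Conclusion.** The point holds as one of efficiency and labelling. Applied as written, the general rule would discard baseline, strata and repeated measures for quality of life. The variance of each comparison could be 16% to 36% lower with baseline adjustment alone, given an assumed correlation of 0.4 to 0.6. Late comparisons are among survivors and should be described as such. The direction and size of any survivor bias cannot be derived from the documents; it is zero if mortality is equal (with the same kind of patient dying in each arm) or unrelated to quality of life. Quality of life carries no power claim and has no part in the non-inferiority decision, so the primary CCI conclusion does not change.

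**What to change.** State, in the SAP or as a sentence in Statistical analysis, that the general t-test/Mann–Whitney rule does not govern quality of life. Instead, EQ-5D-5L, QLQ-C30 and PAN-26 scores from 1 to 36 months are compared with a longitudinal model that has treatment-by-visit terms and adjusts for the baseline score and the randomisation strata.

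Label the late comparisons as while-alive and show them beside survival by arm. A likelihood-based mixed model in effect projects scores past death, so the SAP should say how its late-visit means are to be read, or fit the model to scores of patients alive at each visit with an independence working correlation and robust standard errors.

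An analysis that includes death, such as a composite or worst-rank comparison, is an optional sensitivity analysis. It mixes survival with quality of life, and statisticians differ on whether it should lead.

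The cost is SAP wording and modest extra programming. Baseline scores, strata and survival are already collected, and the sample size does not change.

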**Methods/design:**

The DIPLOMA-2 trial is an international randomized controlled, patient-blinded, non-inferiority trial performed in 14 high-volume pancreatic centers in Europe with a minimum annual volume of 30 MIPD and 30 OPD. A total of 288 patients with an indication for elective pancreatoduodenectomy for pre-malignant and malignant disease, eligible for both open and minimally invasive approach, are randomly allocated for MIPD or OPD in a 2:1 ratio. Centers perform either laparoscopic or robot-assisted MIPD based on their surgical expertise. The primary outcome is the Comprehensive Complication Index (CCI®), measuring all complications graded according to the Clavien-Dindo classification up to 90 days after surgery. The sample size is calculated with the following assumptions: 2.5% one-sided significance level (α), 80% power (1-β), expected difference of the mean CCI® score of 0 points between MIPD and OPD, and a non-inferiority margin of 7.5 points. The main secondary outcome is time to functional recovery, which will be analyzed for superiority. Other secondary outcomes include post-operative 90-day Fitbit™ measured activity, operative outcomes (e.g., blood loss, operative time, conversion to open surgery, surgeon-reported outcomes), oncological findings in case of malignancy (e.g., R0-resection rate, time to adjuvant treatment, survival), postoperative outcomes (e.g., clinically relevant complications), healthcare resource utilization (length of stay, readmissions, intensive care stay), quality of life, and costs. Postoperative follow-up is up to 36 months.

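### The general Kaplan–Meier rule, read plainly, also covers time to start of adjuvant therapy, where death is a competing event; a minor correction to a secondary outcome

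*Protocol article*

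**What the plan says.** The abstract of the protocol article (Methods/design) names among the oncological outcomes "R0-resection rate, time to adjuvant treatment, survival". Secondary outcomes lists the start of adjuvant therapy together with its timing, "time to) start of adjuvant therapy", in the group introduced as "postoperative outcomes (up to 90 days after surgery; major complications".

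Statistical analysis then gives the general rule "Time to event endpoints, such as survival, will be calculated using Kaplan–Meier estimations". Survival is an example there, not the limit of the rule. The sentences that follow turn to Cox regression for survival.

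Death before an event is mentioned once, for time to functional recovery: "Secondary analysis will include correction for censored patients (death before time to functional recovery obtained". That outcome also has its own test (Gehan–Breslow or log-rank). No competing-risk method is named for any outcome.

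Receipt of adjuvant therapy also appears as a yes/no outcome: "Furthermore, predictors for receiving adjuvant chemotherapy or readmission will be assessed". Under the same section, categorical variables are reported as proportions.

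**The concern.** Overall survival has no competing event, but adjuvant start does. Kaplan–Meier with deaths censored treats patients who died as if they would have gone on to start at the rate of those still alive. The curve then estimates uptake in a population without deaths, which is always at least as high as the uptake that occurs.

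Two features make this relevant here. Background names greater use of adjuvant chemotherapy as a possible advantage of the minimally invasive approach (MIPD). Background and Discussion also say that doubt about mortality after laparoscopic MIPD in an earlier trial is a reason for this one. If MIPD did have more early deaths, this estimator would remove their effect from an outcome that the rationale counts in favour of MIPD.

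**Working it through.** **Inputs from the article.** The arms have 192 and 96 patients (Sample size calculation). The window of the list that holds this outcome is 90 days (Secondary outcomes). The mortality scenario is 5 deaths (10%) versus 1 (2%), P = 0.20, from an earlier laparoscopic trial (Discussion). The article gives no figure for adjuvant therapy, so there is none to reproduce.

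**Assumptions.** K, the value of 1−KM at 90 days with deaths censored, is 30% to 80% and equal in both arms. D, mortality without prior adjuvant start, is 2%, 5% or 10%. The share of patients with malignancy is 60% to 100%.

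**Upper case: all deaths precede the first start.** Cumulative incidence = K × (1 − D), so the overstatement is K × D. At K = 60%:
- D = 10%: 0.60 × 0.90 = 54.0%, overstated by 6.0 points.
- D = 2%: 0.60 × 0.98 = 58.8%, overstated by 1.2 points.
- 1−KM shows 60% in both arms and hides 58.8 − 54.0 = 4.8 points.

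**Lower case: constant hazards of starting and dying over 90 days.** Let a = −ln(1 − K) and d = −ln(1 − D). Cumulative incidence = a/(a + d) × [1 − (1 − K)(1 − D)]. At K = 60%, a = 0.916:
- D = 10%: d = 0.105; 0.897 × 0.640 = 57.4%, overstated by 2.6 points.
- D = 2%: d = 0.0202; 0.978 × 0.608 = 59.5%, overstated by 0.5 points.
- Hidden difference: 59.5 − 57.4 = 2.1 points.

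A simulation of the constant-hazard case with 400,000 patients per scenario agreed: 59.9% versus 57.3% at 10% deaths, and 60.0% versus 59.5% at 2%.

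**Range of overstatement** (lower case at K = 30% to upper case at K = 80%):

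| Deaths | Overstatement, points |
|---|---|
| 2% | 0.3 to 1.6 |
| 5% | 0.7 to 4.0 |
| 10% | 1.4 to 8.0 |

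**Hidden difference against its standard error (SE)**, upper case at K = 60%. SE = √[p₁(1 − p₁)/n₁ + p₂(1 − p₂)/n₂].
- 100% malignancy: √[0.540 × 0.460/192 + 0.588 × 0.412/96] = 6.2 points; 4.8/6.2 = 0.8 SE.
- 60% malignancy (n = 115.2 and 57.6): SE = 8.0 points; 4.8/8.0 = 0.6 SE.

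At the top of the assumed range, K = 80%, the upper case gives 72.0% versus 78.4%. That is 6.4 points against an SE of 5.3 to 6.8, or about 0.9 to 1.2 SE.

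**The case against.** The strongest objection is that the article never completes the chain. It does not say that adjuvant start is analysed by Kaplan–Meier, that death is censored for it, or that uptake is read from 1−KM. Survival is the only example given, and the censoring wording belongs to functional recovery, where a correction is promised. A detailed analysis plan is due before database lock. This stands as a limit: the application to adjuvant start is an inference from general wording. It does not remove the point, because what is at issue is a stated general rule that does not suit one of the article's own endpoints, not an omitted detail.

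A reader might infer that Kaplan–Meier is the only rule for time-to-event outcomes. It is not, since functional recovery has its own test.

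A reader might also infer that reported uptake must conceal excess deaths. The article does not support that. Start as a yes/no outcome can be reported as a proportion, which falls with mortality if all operated patients with malignancy are counted. Mortality is itself a secondary outcome, and death scores 100 on the primary outcome. What the proportion leaves open is the timing. Comparing days to start by t-test or Mann–Whitney would use starters only, a group selected after randomization.

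Finally, dividing the 6.0-point shift by the SE of the MIPD arm alone gives about 1.3 to 1.7. The harm in question is a hidden difference between arms, so the SE of the difference is the proper scale.

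**Conclusion.** The point holds in a conditional form and at low severity. Read plainly, the Kaplan–Meier rule covers an endpoint that death makes impossible. If deaths are censored, the probability of starting is overstated. The direction is certain whenever some deaths precede starts. That the overstatement is larger in the arm with more early deaths also requires similar start rates among survivors, which is typical but not guaranteed.

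The size depends on assumed uptake and on when deaths occur. At 2% to 5% mortality it is 0.3 to 4.0 points. The 10% versus 2% contrast rests on 5 deaths against 1 in another trial and is no forecast for this one. Even there, at 60% uptake, the hidden difference is about 2 to 5 points, well within sampling error for these arm sizes.

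**What to change.** In Statistical analysis, limit the Kaplan–Meier sentence to overall survival. For time to start of adjuvant therapy, in operated patients with malignancy, report the cumulative incidence per arm with death before start as a competing event (Aalen–Johansen estimator). Compare arms by the difference in cumulative incidence at a fixed day or by Gray's test. Count patients who never start as not started rather than censoring them.

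The cost is a sentence of wording and standard software. Mortality is already recorded. Reported uptake will be slightly lower than under Kaplan–Meier.
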